## Abstract

**Background:**

Although glucocorticoids are widely used in the treatment of patients with early rheumatoid arthritis, the best dosage of glucocorticoids with regards to efficacy and safety is not known.

The aim of the study ‘Comparison of the efficacy and safety of two starting dosages of prednisolone in early active rheumatoid arthritis’ (CORRA) is to compare two standard glucocorticoid starting dosages and the non-use of glucocorticoids in the treatment of patients with early active rheumatoid arthritis on the background of the established ‘anchor’ therapy with methotrexate.

**Methods/design:**

CORRA is an investigator-initiated, randomized, multicenter, double-blind, placebo-controlled trial with two treatment arms, starting with 60 mg or 10 mg prednisolone per day, tapered down to 5 mg prednisolone within eight weeks, and one placebo arm, each arm comprising 150 patients. The duration of the intervention is 12 weeks. In parallel, all patients will be treated with methotrexate (usual dosage 15 mg/week). The primary efficacy endpoint is the progression of radiographic joint damage after one year compared to baseline. Important secondary endpoints are the percentage of patients in remission, patient global assessment of disease activity, and changes of functional capacity. Safety monitoring is performed.

The statistical analysis is performed in three hierarchical steps. The first step is an analysis of covariance (α = 0.05) to compare the group with the initial prednisolone dosage of 60 mg and the placebo group. In case of a statistically significant result, the comparison of the group starting with 10 mg prednisolone with the placebo group will be performed as a second step (α = 0.05). In case of superiority of the 10 mg prednisolone group versus the placebo group, the third step will be a non-inferiority test for the 10 mg prednisolone group versus the 60 mg prednisolone group (α = 0.025).

**Discussion:**

The CORRA trial will yield information concerning the optimal glucocorticoid dosage schedule in the treatment of patients with early rheumatoid arthritis.

**Trial registration:**

This trial was registered on 19 November 2013 at ClinicalTrials.gov. Registration number: NCT02000336.

## Background

Rheumatoid arthritis (RA) is a chronic disease characterized by inflammation of the peripheral joints leading to disability, impaired functioning, and premature death. Irreversible joint damage may occur very soon after disease onset. The most important treatment strategy is the early use of disease-modifying antirheumatic drugs (DMARD). However, DMARD have a delayed onset of efficacy and side effects may require cessation of treatment.

Glucocorticoids (GC) are fast-acting anti-inflammatory drugs, now also considered as disease modifying because of their ability to decelerate structural damage [1]. Especially during the first weeks of DMARD treatment, GC are frequently used due to the rapid onset of their anti-inflammatory efficacy. However, it is well known that GC may have considerable side effects such as osteoporosis, diabetes mellitus, arterial hypertension, cardiovascular events, glaucoma, tuberculosis, and weight gain [2]. Hoes *et al*. [3] systematically analyzed the literature on reported adverse events (AE) and found the risk of AE to be 43 per 100 patient-years (95% confidence interval (CI): 30 to 55).

There is good evidence of clinical, functional, and structural efficacy for: 5 to 10 mg prednisolone (PRED)/day over two years [4–7]; and initial dose of 60 mg PRED, tapered to low or zero dose over six to eight months [8, 9] given in addition to DMARD [10]. However, in most rheumatology departments a dosage of 60 mg PRED is not used in the treatment of RA due to toxicity concerns. With the common implementation of ’treat-to-target’ strategies [11], including higher doses of DMARD and a more rapid dose escalation, the percentage of patients undergoing concomitant GC treatment over a long period may diminish. Thus, within a treat-to-target setting, lower dosages of PRED taken over a short period may render sufficient disease modification. Usually, a low (<7.5 mg PRED equivalent a day) to medium (>7.5 mg but <30 mg PRED equivalent) [12]) dose GC schedule is thought to provide sufficient benefit [13]. Following the European League Against Rheumatism (EULAR) recommendations [14], the dose is often tapered as rapidly as is clinically feasible [15].

Therefore, most rheumatologists rather use 7.5 to 10 mg PRED in the initial treatment of RA, increasing the dose in case of lack of efficacy, and tapering the dose over the following weeks to bridge the interval until DMARD become clinically efficacious. Unfortunately, there is insufficient data concerning this dosage schedule.

In order to shed further light on the best possible GC treatment strategy in early RA regarding both efficacy and safety, we have designed a study which may guide future treatment decisions.

The main aims of this study are: to compare the use of GC as a bridging therapy with placebo in a treat-to-target setting with DMARD, and to define the best out of two standard GC dosage regimens. Both aims are with regard to the progression of radiographic joint damage after one year compared to baseline.

## Methods/Design

### Trial design

CORRA is a multicenter, randomized, placebo-controlled, double-blind clinical trial conducted in 30 rheumatology practices in North Rhine-Westphalia, Germany. Most of these practices are members of the RheumaNetz Westfalen-Lippe, a local cooperation of rheumatologists in the eastern part of North Rhine-Westphalia. In total, 450 patients with early active RA will be randomized to receive one of two GC treatments (starting with 10 or 60 mg PRED, tapered down to 5 mg PRED within eight weeks) or placebo, each arm comprising 150 patients. The duration of the intervention is 12 weeks. In parallel, all patients start medication with methotrexate (MTX), at a usual dosage of 15 mg/week. The primary efficacy endpoint is radiographic joint damage after one year compared to baseline. Important secondary endpoints are the percentage of patients in remission, patient global assessment of disease activity, and changes of functional capacity. Safety monitoring is performed.

The study is approved by the local ethic committees Ethik-Kommission der Ärztekammer Westfalen-Lippe und der Medizinischen Fakultät der Westfälischen Wilhelms-Universität Münster (leading ethic committee: 2013-250-f-A), Ethik-Kommission der Ärztekammer Nordrhein, Dusseldorf, and Ethikkommission bei der Ärztekammer Niedersachsen, Hannover. It is registered at the European Union Drug Regulating Authorities (EudraCT: 2012-004074-25), at ClinicalTrials.gov (NCT02000336), and German Clinical Trials Register (DRKS-Nr: DRKS00004774). The principles of good clinical practice will be an essential component of the trial. It will be conducted in accordance with the Declaration of Helsinki. All patients will be required to give written informed consent before inclusion in the study.

### Participants

The 2010 RA classification criteria established by the American College of Rheumatology/EULAR collaborative initiative will be used in this trial to enable the early diagnosis of RA [16]. In general, most patients enrolled in this trial will be seen by a rheumatologist early in the course of their disease. To meet the circumstances of routine rheumatology care where patients are sometimes seen with a delay of many months, patients with a disease duration of up to three years may be enrolled. In general, patients will be MTX naïve (MTX pretreatment of four weeks or less is allowed).

To outweigh the risks of MTX and GC treatment, RA activity must be moderate or high as measured by a Disease Activity Score 28 (DAS28) of >4. The DAS28 score is a compound score comprising the number of tender joints (out of 28), swollen joints (out of 28), the erythrocyte sedimentation rate (ESR, after 1 hour), and the patient’s assessment of disease activity. The range of the score is 0 (no activity) to 10 (maximum disease activity) [17]. In patients with a pain disorder such as fibromyalgia, the DAS28 score may be unduly elevated because of the high number of tender joints. To ensure a sufficient amount of inflammatory disease activity, the number of swollen joints should be three or more for a patient to be enrolled in the trial.

Key exclusion criteria will ensure that no patients with very high risks for GC or MTX toxicity will participate in the trial. The exclusion criteria are in accordance with standard rheumatological decision-making and therefore do not promote undue patient selection for this study.

To avoid an inappropriate risk of MTX toxicity, it is mandatory to exclude patients with severe liver disease, active hepatitis B or C viral infection, renal disease (creatinine clearance <30 ml/minute), clinically relevant hematological disease, relevant immunodeficiency including HIV infection, clinically significant pulmonary fibrosis, complicated gastric or duodenal ulcer, a history of malignant melanoma, pregnancy or planned pregnancy, or severe infections within the previous six weeks before study participation.

Patients with uncontrolled diabetes mellitus, arterial hypertension, or intraocular pressure should not receive GC treatment and are therefore excluded as well. On general grounds, non-compliant patients and patients outside the range of 18 to 80 years will not be allowed to participate.

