### Primary outcome parameter

One of the best evaluated and relevant outcome measures in the assessment of RA is the radiographic joint damage as measured by the van der Heijde modification of the Sharp score (SHS) [21]. This score reflects the structural damage caused by the inflammatory joint disease.

Radiographic joint damage, as assessed by the SHS or other scoring systems, correlates with physical function [22], employment status [23], and mortality [24]. The effects discussed in the literature are comparable to the effects assumed for this study. According to the ‘window of opportunity’ concept, reduced radiological damage early in the course of RA leads to a beneficial modification of the long-term outcome. Therefore, the primary outcome parameter will be the progression of radiographic joint damage after one year compared to baseline measured by the SHS.

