### Blinding and statistical methods

All participating rheumatologists and radiologists will be blinded against the interventions, thus assuring blinded assessment of outcome variables.

The primary endpoint is the progression of radiographic damage after one year compared to baseline (measured by the SHS). Analysis will be performed in three steps to compare the three groups (Pl: placebo group; V10: group starting with 10 mg PRED; and V60: group starting with 60 mg PRED). Primary analysis will be conducted by analysis of covariance (ANCOVA) for V60 versus Pl, using baseline values as covariates and 12-month values as dependent variables. In case of a statistically significant result (α = 0.05), a comparison of V10 versus Pl will be performed (α = 0.05). In case of superiority of V10 versus Pl, a non-inferiority test for V10 versus V60 will be performed (α = 0.025), as is shown in Figure 2. A non-inferiority margin of 1.3 SHS points has been selected.

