## Discussion

The most frequently used dosage of 7.5 to 10 mg PRED as a bridging treatment in early RA is a compromise between the good clinical short-term effect of GC and the attempt to minimize the risk of AE. However, the first months of RA are considered to be like a window of opportunity, with the best offer to change the course of the disease. This window of opportunity should be used to ‘hit hard and early’ (provide aggressive treatment as soon as possible) [14]. It may well be that higher dosages of GC, as used in the COBRA study [8] and the BeSt-study [9], have a higher impact on the outcome without a considerable increase of AE. The answer to this question would be highly relevant for the individual patient because of the increased possibility to induce a more favorable course of the disease. The immediate benefits for society in general and for the economic expenditures in particular are obvious.

The aim of our study is to test different treatment strategies rather than to evaluate the dose-dependent effect of PRED on the Sharp score. This means to find answers to two questions. Firstly, is it worthwhile to start with a high-dose PRED treatment in active RA patients, even if a treat-to-target approach is followed? Secondly, is there any difference between initially high and low PRED doses in the sense of benefit in radiographic progression? In the further course, there are many potential confounders, such as imbalanced MTX use, imbalanced GC use during weeks 13 to 52, and imbalanced use of biologics. These imbalances may flaw the immediate effect of the PRED bridging on the Sharp score, but have only a minor impact on the tested treatment strategies. The possible results of our testing procedure may clarify if high-dose PRED bridging is not superior to a placebo, then the disease modifying effect of PRED no longer plays a major role in a treat-to-target setting. If there is a significant difference between high-dose PRED bridging and placebo, and low-dose PRED bridging is not superior to a placebo, then high-dose bridging may be strongly recommendable. If a low-dose bridging compares to a significantly effective high-dose bridging, the EULAR recommendation of merely regarding the symptomatic effect of PRED is confirmed. If there are no differences between all three groups even with sufficiently imbalanced concomitant therapies, then only symptomatic effects of PRED should guide treatment decisions.

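### Disease duration, which ranges up to three years at entry, is not used in the stated primary ANCOVA or in any other analysis the article describes; adding it is a free improvement that would also make a null result easier to read

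*Protocol article*

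**What the plan says.** Under Participants, the article expects that "most patients enrolled in this trial will be seen by a rheumatologist early in the course of their disease". It then widens entry and gives late referral as the reason: "To meet the circumstances of routine rheumatology care where patients are sometimes seen with a delay of many months". The limit it sets on these grounds is that "patients with a disease duration of up to three years may be enrolled". All entrants must have active disease (DAS28 above 4, three or more swollen joints) and little or no previous methotrexate.

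The aims in the Background are broad. The first is "to compare the use of GC as a bridging therapy with placebo in a treat-to-target setting with DMARD". The Discussion adds: "The aim of our study is to test different treatment strategies rather than to evaluate the dose-dependent effect of PRED on the Sharp score".

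Time since onset enters through the rationale. Primary outcome parameter argues that "reduced radiological damage early in the course of RA leads to a beneficial modification of the long-term outcome". The Discussion is narrower: "the first months of RA are considered to be like a window of opportunity". It also says in advance how a failure at step one would be read: if high-dose bridging does not beat placebo, disease modification by prednisolone no longer matters much under treat-to-target.

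Under Blinding and statistical methods, the primary comparison is an ANCOVA "using baseline values as covariates and 12-month values as dependent variables". Randomisation is blocked by centre. The one additional adjusted analysis of the primary endpoint (Secondary outcome parameter) uses mean methotrexate dose, biologicals, and mean glucocorticoid dose in weeks 13 to 52, all measured after randomisation. Duration appears in none of these.

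**The concern.** Baseline SHS is the damage accumulated so far. Without the time over which it accumulated, it says little about its rate. A score of 6 after 4 months is about 6 / (4/12) = 18 points per year; the same score after 36 months is 6 / 3 = 2 points per year. A model with baseline SHS alone treats these two patients alike. If the earlier rate carries forward, duration holds information that the model leaves out.

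The second issue is interpretation. If bridging works mainly in the first months, later entrants pull the average contrast with placebo toward zero. A non-significant step one closes the whole hierarchy, and the Discussion would then read it as evidence against a disease-modifying role. None of the analyses in the article would help to tell a true absence of effect from an average over early and late patients. Dilution would also shrink a true difference between the two prednisolone arms, which makes the 1.3-point margin in step three easier to meet, although step three is reached only after two superiority tests succeed.

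**Working it through.** **Inputs from the article (Sample size).** Effect after dropout 3.5 SHS points, SD 7.5, 150 per arm, two-sided α = 0.05, stated power above 0.95.

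**Reproducing the stated power.** SE = 7.5 × √(2/150) = 0.866. Power ≈ Φ(3.5/0.866 − 1.96) = Φ(2.08) = 0.981; the non-central t distribution also gives 0.981. The stated figure holds.

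**Dilution.** Two quantities are not in the article and are assumed: q, the share of patients outside the window, and r, the fraction of the effect they keep. The average effect is 3.5 × [1 − q(1 − r)].

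| q | Effect, r = 0 | Power | Effect, r = 0.5 | Power |
|---|---|---|---|---|
| 10% | 3.15 | 0.95 | 3.32 | 0.97 |
| 20% | 2.80 | 0.90 | 3.15 | 0.95 |
| 25% | 2.63 | 0.86 | 3.06 | 0.94 |
| 30% | 2.45 | 0.81 | 2.98 | 0.93 |
| 40% | 2.10 | 0.68 | 2.80 | 0.90 |
| 50% | 1.75 | 0.52 | 2.63 | 0.86 |

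With r = 0, power of 0.90 needs an effect of 0.866 × (1.960 + 1.282) = 2.81, so q = 1 − 2.81/3.5 ≈ 20%. Power of 0.80 needs 0.866 × (1.960 + 0.842) = 2.43, so q ≈ 31%.

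**Precision.** The SE after adjustment is 0.866 × √(1 − R²), where R² is the partial R² of duration given baseline SHS. It is not in the article and is assumed here.

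| Partial R² | SE | Power at effect 3.5 |
|---|---|---|
| 0 | 0.866 | 0.981 |
| 0.01 | 0.862 | 0.982 |
| 0.05 | 0.844 | 0.986 |
| 0.10 | 0.822 | 0.989 |

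The gain counts for more where dilution has already cost power. At q = 40% and r = 0, a partial R² of 0.10 raises power from 0.68 to 0.72.

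To see which values are plausible, one can simulate a yearly damage rate that is log-normal (median 4 points, log-SD 0.8 to 1.1) with duration between 0.1 and 3 years, and compare the residual SD with and without duration. The SE falls by about 0 to 3% when the pre-entry rate persists weakly or moderately into the trial year, and by about 6 to 20% when it persists fully. Precision was not lost in any setting tried. These inputs are assumptions, so the range matters more than any single value.

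**Is an early-group estimate informative?** At effect 3.5 and SD 7.5, if 80 / 70 / 60 / 50% of each arm is early, the comparison within that group has power 0.95 / 0.92 / 0.88 / 0.82.

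**The case against.** The strongest reply is that the population fits the stated aim. The aims concern bridging strategies in early active disease. The first months are named as the window only in the Discussion, as rationale, and not in any hypothesis. Wide entry has a stated reason, most patients are expected early, and late entrants still have active, essentially methotrexate-naive disease. All of this stands. A reader might infer that the entry criterion contradicts the trial's hypothesis; the article does not support that.

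A reader might also infer that the effect is diluted. The article gives no distribution of duration, no cut-off for the window and no effect by duration. The zero-effect case has no source in it, and a 50% share outside sits badly with the expectation that most patients are early. Where half the effect is kept, power stays at about 0.90 or more up to 40% outside.

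Nor can one conclude that duration will never be examined. The article condenses a fuller plan, and supportive subgroup analyses are commonly left to that plan. Omitting a prognostic covariate does not bias a randomised comparison either. The Discussion also tempers its own reading: results are to be weighed with other endpoints, and a confirmatory trial may be needed.

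What remains is that the primary model is stated, and a baseline factor tied to the trial's own rationale is not in it.

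**Conclusion.** This is a free improvement and not an error. The stated ANCOVA is valid, and the entry criterion is consistent with the aim. Leaving duration out has two modest costs. The first is precision: an SE about 0 to 3% higher than it need be under weak or moderate persistence of the pre-entry rate, and more under strong persistence. At the planned effect this moves superiority power by about one percentage point at most for a partial R² up to 0.10. The second is interpretation: after a null step one, no analysis in the article would show whether early patients differed from later ones. The power cost of late entrants depends on two unknowns, their share and the effect they keep. With 25% outside the window it runs from 0.86 (no effect there) to 0.94 (half the effect), against 0.98 with none outside.

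**What to change.** Keep the entry criterion as it is. Then:

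1. Pre-specify disease duration at randomisation, or its logarithm, as a covariate alongside baseline SHS in the primary ANCOVA, in all three steps. Fix the definition of onset for this covariate before unblinding, without changing who is eligible.
2. Report, as supportive only, the treatment-by-duration interaction and the V60 versus placebo and V10 versus placebo differences with 95% CIs by duration. If duration is grouped, set the cut-off in advance. Read these estimates alongside the Discussion's conclusion for a null step one. They should not become a condition for that conclusion, since no criterion for absence of benefit in a subgroup has been set.

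The cost is one degree of freedom in the primary model and wide intervals for the duration-specific estimates. Duration has to be determined to apply the three-year limit, and inclusion criteria are monitored in 100% of data, so the variable should be on hand. The article does not say that it is recorded as a date or a continuous value, and this should be confirmed.

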### Study medication, randomization, and follow-up

The intervention phase will last 84 days. The respective PRED dosages of the treatment groups are listed in Table 1.

**Table 1 Tab1:** **Schedule of the prednisolone dosage (mg/day) of the three study arms of the CORRA study**

Day	Placebo	V10	V60
1 - 7	0	10	60
8 - 14	0	10	40
15 - 21	0	10	25
22 - 28	0	10	20
29 - 35	0	7,5	15
36 - 42	0	7,5	10
43 - 49	0	7,5	7,5
50 - 56	0	7,5	7,5
57 - 84	0	5	5

CORRA: Comparison of the efficacy and safety of two starting dosages of prednisolone in early active rheumatoid arthritis, PRED: prednisolone, V10: group starting with 10 mg PRED; V60: group starting with 60 mg PRED.

In parallel, all patients will start MTX medication at a usual dosage of 15 mg/week (modifications may be made by the rheumatologist, for example due to minor renal insufficiency or age).

Patients are seen every four weeks within the first three months. In case of lack of efficacy, the MTX dose will be increased to 20 mg/week and further up to 25 mg/week, after four or eight weeks, respectively. In the further course of the study, a change of DMARD medication according to the EULAR recommendations [14] is allowed in case of lack of efficacy and/or intolerable side effects. These decisions are made by the treating rheumatologist based on the treat–to-target paradigm for RA [11].

Study visits will take place at baseline and after 4, 8, 12, 24, and 52 weeks (Figure 1). Physical examination, determination of DAS28, and safety measures including lab examinations will be performed at every visit. Radiographs of hands and feet will be done at baseline and after one year. Functional assessments including the EuroQol-5D [18], Patient Health Questionnaire-2 [19], and physical functioning questionnaire Hannover (FFbH) [20] are planned at baseline and after 12, 24, and 52 weeks. Dual-Energy X-ray Absorptiometry (DXA) of the lumbar spine and hip at baseline and after 24 weeks is planned in case of at least one of the following: age >60 years for men, >50 years for women, current smoker, history of non-traumatic fracture, parental history of hip fracture (Table 2).

